## 3. Method

- 1) Survey period: 12 weeks (August 2017-February 2018)
- 2) Test method: Epidemiological survey, clinical trial (randomized open trial)
- 3) Number of cases: 60 cases (30 women who take equol + lactobionic acid supplement, and 30 women who do not take the supplement)
- 4) Test food: "Equol + lactobionic acid" 3 tablets (10 mg) daily (marketed in December 2013)

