## 4. Measures

Before ingesting the supplement: Equol check (in urine), gut microbiota test (stool test), dietary habit assessment (BDHQ).

Before and after ingestion of supplement: height / weight / body composition, blood test (TG, HDL-C, LDL-C, T-CL, uric acid, HbA1C), baPWV, visceral fat CT test (fat scan), AGE measurement by AGE reader, and climacteric system assessments.

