## 5. Outcome evaluation

- 1) Primary Outcomes: blood test (TG, HDL-C, LDL-C, T-CL, uric acid, HbA1C), baPWV, visceral fat area
- 2) Key Secondary Outcomes: AGE, relationship between equol-producing ability, type of intestinal bacteria, and dietary habit assessment (BDHQ) from the test results, safety of supplement, climacteric symptoms

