## 7. Analysis

For the primary measures, perform chi-squared test and t test for comparison between groups and before and after the study period. For secondary outcomes, anonymized data are entered into the database and the correlation is analyzed. Drop out cases and missing values are not included in the analysis. Other questionnaire surveys will be conducted according to the evaluation criteria of each questionnaire. The visceral fat CT examination and baPWV measurement at the start of the test and at 12 weeks will be performed at the same site in order to eliminate measurement errors.

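### Section 7 names a between-group t test with no baseline covariate and does not say whether week-12 values or changes are compared; ANCOVA on the week-0 value is a nearly free improvement

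*Protocol*

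**What the plan says.** Section 7 (Analysis) tells the analyst, for the primary measures, to "perform chi-squared test and t test for comparison between groups". The sentence does not stop there; in full, the instruction is to "perform chi-squared test and t test for comparison between groups and before and after the study period". No model, covariate or baseline adjustment is named. The sentence does not say which quantity enters the between-group test: the week-12 value or the change from week 0.

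Section 5 lists the outcomes concerned: "Primary Outcomes: blood test (TG, HDL-C, LDL-C, T-CL, uric acid, HbA1C), baPWV, visceral fat area". That is eight measures, all continuous.

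Section 4 places all eight both before and after the supplement: "blood test (TG, HDL-C, LDL-C, T-CL, uric acid, HbA1C), baPWV, visceral fat CT test (fat scan". The schedule in section 6 marks the blood test, baPWV and the visceral fat scan at week 0 and week 12. Section 7 itself mentions the "visceral fat CT examination and baPWV measurement at the start of the test and at 12 weeks".

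Section 3 describes a "clinical trial (randomized open trial" with "60 cases (30 women who take equol + lactobionic acid supplement, and 30 women who do not take the supplement". It describes no stratification or other balancing on baseline values.

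**The concern.** With 60 women, precision is the scarce resource. The week-0 value of each primary outcome will already be in the database and is usually the best single predictor of the week-12 value. A t test on week-12 values ignores it. A t test on change subtracts the whole of it, which is too much whenever the correlation between visits is below 1 and the spread is similar at both.

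Two things are at stake. The first is power: either t test needs more women than ANCOVA to detect the same difference. The second is chance imbalance. If the arms happen to differ at week 0, both t tests give an estimate that is biased given that imbalance, in opposite directions.

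The silence on week-12 value versus change adds to this. The two tests can give different answers on the same data, and in an open trial the choice should not remain available once results are seen. The within-arm before/after tests do not help, because they do not compare the arms.

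**Working it through.** **Inputs from the protocol.** 30 women per arm (section 3); eight continuous outcomes (section 5), each measured at weeks 0 and 12 (sections 4 and 6).

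**Assumptions, because the protocol gives no figure.** Two-sided 5% level; equal SD at both visits, set to 1; a linear relation between visits; correlation r from 0.3 to 0.9, with 0.5 to 0.8 as the working range; all 60 women analysed.

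**The protocol's own figure.** The 60 women are given without power, effect size or SD, so the number cannot be reproduced. Read backwards, 30 per arm gives a two-sample t test 80% power for a difference of 0.736 SD (0.723 SD by normal approximation).

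**Variance of the treatment difference**, relative to a t test on week-12 values:
- t test on week-12 values: 1
- t test on change: 2(1 − r)
- ANCOVA on the week-0 value: 1 − r²

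ANCOVA relative to the change test is therefore (1 − r²) / [2(1 − r)] = (1 + r)/2. The number of women that 60 are worth is 60 divided by the relevant ratio.

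| r | Change t test | ANCOVA (= ratio to week-12 test) | 60 women worth, vs week-12 test | ANCOVA / change test | 60 women worth, vs change test |
|---|---|---|---|---|---|
| 0.3 | 1.40 | 0.91 | 66 | 0.65 | 92 |
| 0.5 | 1.00 | 0.75 | 80 | 0.75 | 80 |
| 0.7 | 0.60 | 0.51 | 118 | 0.85 | 71 |
| 0.8 | 0.40 | 0.36 | 167 | 0.90 | 67 |
| 0.9 | 0.20 | 0.19 | 316 | 0.95 | 63 |

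**Cost of ANCOVA.** One degree of freedom (57 instead of 58) and an expected variance inflation of 1 + 1/56 = 57/56, about 2%. The table leaves this out. Allowing for it, ANCOVA still beats the week-12 test once r² exceeds 1/57, that is r above 0.13. It beats the change test while (1 + r)/2 is below 56/57, that is r below 0.965.

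**Detectable difference at 80% power**, 0.736 SD times the square root of the variance factor, and **power for an illustrative 0.5 SD effect** (noncentral t, ANCOVA cost included in the power):

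| r | Detectable: week-12 / change / ANCOVA (SD) | Power: week-12 / change / ANCOVA |
|---|---|---|
| 0.5 | 0.74 / 0.74 / 0.64 | 48% / 48% / 59% |
| 0.7 | 0.74 / 0.57 / 0.53 | 48% / 69% / 75% |
| 0.8 | 0.74 / 0.47 / 0.44 | 48% / 85% / 88% |

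At the ends of the range, power is 48% / 36% / 51% at r = 0.3 and 48% / 99% / 99% at r = 0.9.

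**Chance imbalance.** The standard error of the week-0 difference is √(2/30) = 0.258 SD. For any one outcome, a gap above 0.25 SD has probability 33%, and a gap above 0.5 SD has probability 5.3%. Given a gap g, the week-12 test is biased by r·g and the change test by −(1 − r)·g. With g = 0.5 SD and r = 0.7, the type I error given that gap is about 20% for the week-12 test and 10% for the change test, against 5% for ANCOVA. With g = 0.25 SD it is 3.6% and 4.8%, so the inflation appears only with the larger, rarer gaps.

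**The case against.** The strongest reply is that nothing in section 7 is wrong. In a randomized trial the t test is valid, and its type I error over all possible allocations is 5%. A reader might infer from the imbalance figures that the primary analysis is biased or its error rate inflated. The protocol does not support that: the inflation is conditional on a large gap that occurs about one time in twenty per outcome. This part of the objection stands.

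A second reply concerns size. A reader might take 118 or 167 women as the amount lost. Those figures assume that week-12 values are compared. The sentence in section 7 also refers to before and after, so a t test on change is an equally natural reading. On that reading 60 women with ANCOVA are worth only 67 to 80, and at r = 0.9 hardly more than 60. This stands too, and both readings must be shown together. The correlation is also unknown, and at r = 0.3 the gain over the week-12 test is only 9% of variance before the 2% cost.

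A third reply is that covariates are commonly left to a statistical analysis plan, which is not available here. This has less force. The protocol does more than stay silent: it names the test, and names one that leaves the compared quantity open.

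Finally, ANCOVA is not wholly free and relies on a roughly linear relation to baseline. That is true, but the cost is about 2% of variance.

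**Conclusion.** The point holds as a nearly free improvement, not as an error in a stated figure or an invalid analysis. Section 7 fixes a t test, names no baseline covariate and leaves open whether week-12 values or changes are compared, although the baseline of every primary outcome is collected.

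For r between 0.5 and 0.8, ANCOVA has 75% to 36% of the variance of a week-12 t test and 75% to 90% of that of a change-score t test. Which set applies cannot be settled from the protocol. These figures rest on the assumed correlations, equal SDs at the two visits and 30 women analysed per arm. The direction is more secure than the size: over the whole range examined, r from 0.3 to 0.9, ANCOVA is at least as efficient as either t test even after its cost, and the sponsor need not know r in advance to benefit.

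**What to change.** In section 7, replace the between-group t test for the primary measures with a sentence to this effect: each continuous primary outcome is compared between arms by ANCOVA of the week-12 value on arm and the week-0 value of the same outcome, reported as an adjusted mean difference with its 95% confidence interval; before/after tests within each arm are descriptive only.

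This also removes the doubt about which quantity is compared. It needs no new visit, measurement or participant. The cost is one sentence, one degree of freedom and about 2% in variance.

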## **Outline of Research**

### **1. Objective**

To investigate the relationship between dietary status, type of intestinal bacteria, and equol-producing ability.

To examine the effects of ingestion of "equol + lactobionic acid" on various parameters of lifestyle-related disease risk such as arteriosclerosis and visceral fat area including the relationship with the above background factors.

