## **Outline of clinical trial on equol and lactobionic acid supplement**

### **1. Research Objective and Background**

Equol is an active metabolite in which daidzein, a type of soy isoflavone, is metabolized by intestinal bacteria. Its structure is similar to that of the female hormone estrogen, and it has an estrogen-like action, which alleviates menopausal symptoms. , Suppression of bone loss, improvement of lipid metabolism and arteriosclerosis, etc. have been reported, and are expected to be effective for a wide range of women's health care.

On the other hand, the number of people who can produce equol in the body is as small as about 50% in Japan, and it is said that the eating habits, living environment, and intestinal bacteria, which are equol-producing bacteria, are involved in the equol-producing ability.

In this clinical study, it is considered meaningful to investigate and clarify the relationship between dietary habits and the types of intestinal bacteria regarding equol-producing ability.

In addition, we investigated the effects of ingestion of "equol + lactobionic acid" on lifestyle-related disease parameters such as vascular system, visceral fat area, and AGEs (advanced glycation end products) in the above subjects, and investigated the effects of equol production ability and intestinal bacteria. It is important to clarify the relationship with the background factors of equol in order to further build evidence on the action of equol.

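### Section 7 names only correlation for the secondary outcomes, so as written AGE and climacteric symptoms get no between-arm comparison and safety no summary by arm

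*Protocol*

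**What the plan says.** Section 7 of the protocol (Analysis) assigns methods by class of outcome. The primary class is covered by: "For the primary measures, perform chi-squared test and t test for comparison between groups and before and after the study period". The next sentence covers the secondary class: "For secondary outcomes, anonymized data are entered into the database and the correlation is analyzed". A later sentence adds: "Other questionnaire surveys will be conducted according to the evaluation criteria of each questionnaire".

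Section 5 (Outcome evaluation) lists the key secondary outcomes. AGE comes first, followed by the relationship between equol production, gut bacteria and diet, and the list ends "from the test results, safety of supplement, climacteric symptoms". Blood tests, baPWV and visceral fat area are primary.

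Section 3 (Method) describes the design as "Epidemiological survey, clinical trial (randomized open trial") with 30 women taking the supplement and 30 not. Section 1 (Research Objective and Background) states the aim of studying the effect of ingestion on "lifestyle-related disease parameters such as vascular system, visceral fat area, and AGEs (advanced glycation end products"). The Outline of Research, item 1 (Objective), asks for the supplement's effects "including the relationship with the above background factors", meaning diet, intestinal bacteria and equol-producing ability.

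**The concern.** AGE, climacteric symptoms and safety are questions about what the supplement does. In a randomised trial they are answered by comparing the arms. A correlation coefficient describes how two variables move together and estimates no difference between arms. If the analysis follows Section 7, AGE and climacteric symptoms produce no treatment estimate. Adverse events are not set against the untreated arm, which is the only reference the trial has.

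A related question arises for the background factors. Suppose the supplement's effect by equol status is judged by correlating producer status with an outcome or its change. The factor's prognostic role is then mixed with any modification of the effect. A correlation seen among supplement takers could be reported as a better response in producers when untreated women show the same correlation.

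**Working it through.** **Step 1. Set the sections side by side.**

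| Key secondary item (Section 5) | Question it serves | Scheduled (Section 6) | Method named (Section 7) | Arms compared? |
|---|---|---|---|---|
| AGE | Effect of ingestion (Section 1) | Weeks 0, 12 | Correlation | No |
| Equol production, bacteria, diet | Association at baseline | Week 0 | Correlation | Not needed |
| Safety | Effect of the supplement | Weeks 0, 4, 8, 12 | Correlation | No |
| Climacteric symptoms | Effect of the supplement | Weeks 0, 4, 8, 12 | Correlation; scoring by the questionnaire's own criteria | No |

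The named method fits one of the four items. The schedule makes no distinction by arm, so the data for an arm comparison of the other three are already planned.

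**Step 2. Can a correlation with equol status stand in for an effect-by-status contrast?** Take an outcome with SD 1 within cells, half the women producers, and equal arms.

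- *Real modification, no correlation.* Let the cell means be 0 (non-producer, control), 0.8 (non-producer, supplement), 0.8 (producer, control) and 0 (producer, supplement). The arm difference is +0.8 in non-producers and −0.8 in producers, an interaction of −1.6 SD. The mean by status is (0 + 0.8)/2 = 0.4 in non-producers and (0.8 + 0)/2 = 0.4 in producers. The pooled correlation with status is therefore 0. A simulation of 400,000 women gave 0.001.
- *No modification, clear correlation.* Let producers score 0.8 SD higher in both arms. With status coded 0/1 (SD 0.5), r = 0.8 × 0.5 / √(1 + 0.8² × 0.25) = 0.4/1.077 = 0.37 in each arm. The simulation gave 0.37 in both.
- *Arm effect only.* A uniform 0.8 SD supplement effect gave a simulated correlation with status of 0.001.

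So the correlation identifies neither the arm effect nor its dependence on equol status.

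**Step 3. How precise would an interaction be?** The protocol gives no alpha, power, effect size or SD for its 60 women, so there is no power figure to reproduce. The following are assumptions: two-sided 5%, 80% power, no dropout, normal approximation. From the protocol come 30 per arm (Section 3) and about 50% producers (Section 1).

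With a producers and b non-producers per arm, SE = √(2/a + 2/b) in SD units, and the detectable interaction is (1.960 + 0.842) × SE.

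| Producers | a, b per arm | SE | Detectable interaction |
|---|---|---|---|
| 50% | 15, 15 | 0.516 | 1.45 SD |
| 40% (or 60%) | 12, 18 (or reversed) | 0.527 | 1.48 SD |
| 30% | 9, 21 | 0.563 | 1.58 SD |

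For comparison, the detectable overall arm difference is 2.802 × √(2/30) = 0.72 SD. The ratio (1.447/0.723)² = 4.0 means that an interaction of a given size needs four times as many women as a main effect of that size. Power for a 0.8 SD interaction at 50% producers is Φ(0.8/0.516 − 1.96) = 34%.

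**The case against.** The strongest reply is that the correlation sentence is rough translated text. It does not say what is correlated with what, and it may have been meant only for the equol, bacteria and diet item, where it fits. A SAP, not available here, could add arm comparisons. The ambiguity is real and is a reason to clarify the sentence. But the protocol is not silent: it names group comparison for one class and correlation for the other. A SAP comparing arms on AGE would be departing from it or filling in what it failed to say.

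Two further points have some force. The questionnaire sentence suggests that correlation may not be the only rule for climacteric symptoms, but it concerns each instrument's criteria and names no arm comparison. Section 9 sets out how adverse events are recorded, graded and judged for relatedness, so it would be strained to read Section 7 as an instruction to correlate adverse events. Section 9 also gives no summary by arm.

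On background factors, a reader might infer that the objective cannot be answered. The documents do not support that. Equol status is measured at week 0 in a randomised design with follow-up outcomes, so the contrast can be estimated; it is only unnamed. Nor does the gap follow from the secondary-outcome sentence alone. The Objective ties these factors to arteriosclerosis and visceral fat area, and baPWV and visceral fat area are primary outcomes that this sentence does not govern.

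A reader might also infer that the week 4 and week 8 climacteric assessments go unused. Nothing in the protocol limits that analysis to week 12, so this is not shown.

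**Conclusion.** The point holds for the stated analysis. Section 7 names a method that fits one of four key secondary items. As written it plans no between-arm comparison for AGE or climacteric symptoms and no by-arm summary of safety. The case is firmest for AGE, which Section 1 names as a target of ingestion. It is less sharp for climacteric symptoms and safety, where other sections govern scoring and recording but not comparison. These are secondary outcomes and the data are planned, so the defect is one of wording and should be corrected before analysis.

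The background-factor question is separate and subordinate. The objectives ask it, Section 7 names no arm-by-factor contrast, and correlation cannot replace one. Even a proper interaction analysis would be imprecise: 1.45 to 1.58 SD detectable for 50% down to 30% producers, under the assumptions in the working. Exclusion of dropouts and missing values under Section 7 would make it less precise still.

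**What to change.** Replace the single sentence on secondary outcomes in Section 7 with three:

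1. Correlation is used only for the baseline relationship between equol production, intestinal bacteria and diet.
2. AGE and climacteric scores are compared between arms with adjustment for baseline, for example by ANCOVA at week 12, giving the arm difference and its confidence interval. Whether weeks 4 and 8 enter a repeated-measures model can be left to the SAP.
3. Adverse events are reported as counts and proportions by arm.

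Separately, add for the background-factor objective an exploratory arm-by-equol-producer interaction with its confidence interval, in the models for the outcomes that the objective names.

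The cost is wording and a little analysis time; no new measurement is needed. The drawback is that the interaction estimate will be imprecise, so it must be labelled exploratory and a non-significant result must not be read as an equal effect in producers and non-producers.

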##### **② Exclusion criteria**

Persons with a history of allergies to soy foods, dairy products, and brewer's yeast.

- Persons who have started taking medicines or health foods that may have an effect during the test period.

- Those who are receiving HRT or who are taking drugs that may act on hormones.
- Others that the investigating doctor deems inappropriate.

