### ③Cancellation criteria

Clinical research will be discontinued if any of the following applies.

- During the test period, the subject develops serious symptoms and the safety of the supplement becomes questionable.
- When it becomes clear that the subject was affected by continuously consuming the supplement.

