### **3) How to obtain the consent of the subject**

Prior to the start of this clinical study, the principal investigator will explain the following matters to the subject based on the explanatory document, and then obtain the written consent of the subject based on his / her free will.

The following items should be described in the explanatory document.

- ① Participation in the trial
- ② Purpose of clinical research
- ③ Clinical research method (including experimental aspects, subject selection criteria, etc.)
- ④ Scheduled period of participation of subjects in clinical research
- ⑤ Number of subjects planning to participate in clinical research
- ⑥ Expected clinical benefits and risks or inconveniences (if there is no expected clinical benefits of the subject, inform them)
- ⑦ Presence or absence of other treatment methods when using patients as subjects, and the significant benefits and risks predicted regarding the treatment methods.
- ⑧ Treatments that subjects can receive in the event of clinical research-related health hazards
- ⑨ Participation in clinical research is voluntary, and the subject may refuse or withdraw

participation in clinical research at any time. In addition, refusal or withdrawal will not result in any disadvantage to the subject or loss of benefits that would be incurred if the subject did not participate in the clinical study.

⑩ Promptly inform the subject of the continuation of participation in the clinical study when information that may affect the intention of the subject or his / her substitute is obtained.

⑪ Conditions or reasons for discontinuing participation in clinical research

⑫ Monitors, auditors, clinical research review committees, and domestic and foreign regulatory authorities can view the source materials such as medical records. At that time, the personal information of the subject should be protected. In addition, the documents can be allowed to view if the subject has already stamped or signed the consent document.

⑬ The personal information of the subject should be protected even when the results of clinical research are published.

⑭ the detailed information if the subject needs to bear the cost

⑮ The name, job title and contact information of the principal doctor in-charge of this trial or clinical research collaborator (coordinator)

⑯ Medical institution consultation desk to contact if the subject wants more information regarding clinical research and rights of the subject

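### Section 7 deletes drop-outs and missing values from an open randomised trial, so once any woman is lost the groups compared are no longer those randomised, with bias of unknown direction and size

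*Protocol*

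**What the plan says.** Section 7 (Analysis) prescribes chi-squared and t tests for the primary measures, between groups and before versus after, and a correlation analysis for the secondary outcomes. It then states: "Drop out cases and missing values are not included in the analysis". The sentence is not limited to any one outcome.

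Section 3 (Method) describes a randomised open trial with "30 women who take equol + lactobionic acid supplement, and 30 women who do not take the supplement".

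The protocol gives these routes out of the trial:

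- Section 2, Cancellation criteria, first item: "During the test period, the subject develops serious symptoms and the safety of the supplement becomes questionable".
- Section 2, Cancellation criteria, second item: "When it becomes clear that the subject was affected by continuously consuming the supplement".
- Section 11, 3), on consent: "the subject may refuse or withdraw" at any time, which applies to both arms.
- Section 2, Exclusion criteria: "Persons who have started taking medicines or health foods that may have an effect during the test period". This could also remove women from either arm after entry.

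Sections 4 and 6 place the blood tests, baPWV and visceral fat scan at weeks 0 and 12 only. The urine equol test, flora test and dietary questionnaire are done at week 0 only. Climacteric symptoms and safety are assessed at weeks 0, 4, 8 and 12. The protocol contains no statement that women are analysed as randomised, no instruction to measure a woman at week 12 after she stops, and no sensitivity analysis.

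**The concern.** Randomisation makes the two groups of 30 comparable at the start. Deleting women for what happens afterwards gives that up unless the deletions have nothing to do with outcome. The risk is greater here than in a blinded trial because every woman knows her assignment, and because two of the written exits are tied to the supplement. A woman who takes no supplement cannot meet the second cancellation criterion, and the first makes little sense for her. The protocol therefore provides an exit related to tolerability or response in one arm, and section 7 discards those who use it.

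Three secondary outcomes in section 5 are also touched. The relation of equol-producing ability to flora and diet, which is the first stated objective, needs week-0 data only, yet drop-outs are excluded from it. The safety of the supplement would be assessed without women who stopped because of it. Climacteric scores already recorded at weeks 4 and 8 would be thrown away.

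Because the rule is stated outright, it is not a detail left open for a statistical analysis plan. A plan that analysed all randomised women would contradict the protocol.

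**Working it through.** **No figure to reproduce.** The protocol gives 30 per arm but no drop-out rate, SD, effect size or significance level. What follows is illustration under stated assumptions: no true effect, two-sided 5% test, loss in the supplement arm only, outcome in SD units.

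**Standard error of the difference.** √(2/30) = 0.258 SD.

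**Loss fully determined by outcome (correlation 1).** If the fraction *f* at one extreme leaves, the mean of those kept shifts by φ(z_f)/(1 − f), where φ is the standard normal density and z_f its *f* quantile:

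- f = 0.10: 0.1755/0.90 = 0.195 SD
- f = 0.15: 0.2332/0.85 = 0.274 SD

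**Weaker links.** With correlation *r* between the tendency to leave and the outcome, the shift is *r* times this value. The rejection rate is P(|N(bias/0.258, 1)| > 1.96).

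| Correlation | Bias, 10% lost | Rejection | Bias, 15% lost | Rejection |
|---|---|---|---|---|
| 0 | 0 | 5% | 0 | 5% |
| 0.2 | 0.039 SD | 5.3% | 0.055 SD | 5.5% |
| 0.5 | 0.10 SD | about 7% | 0.14 SD | about 8% |
| 1.0 | 0.19 SD | about 12% | 0.27 SD | about 19% |

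**Check by simulation.** Two-sample t tests (40,000 runs) with the lowest-scoring women removed from the supplement arm gave 12.3% (r = 1) and 6.8% (r = 0.5) with 3 of 30 removed. With 5 of 30 removed, slightly more than 15%, they gave 22.2% and 8.3%. The approximation is adequate.

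**A second way to set the assumption.** Let *k* of 30 supplement women be removed, with a mean *m* SD away from those kept. The bias is (k/30) × m:

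- k = 3, m = 0.5 to 1.0: 0.05 to 0.10 SD; simulated rejection 5.4% to 6.4%
- k = 6, m = 0.5 to 1.0: 0.10 to 0.20 SD; simulated rejection 6.2% to 11.2%
- m = 0: about 5% for either k

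**Precision.** At an assumed 80% power, the detectable difference is (1.96 + 0.84) × √(2/n). This gives 0.72 SD with 30 per arm, 0.76 with 27 and 0.81 with 24.

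**Does imputation alone repair it?** Not if loss depends on the week-12 value itself. With 10% lost at r = 1 and an assumed baseline correlation of 0.7, a simulated baseline-adjusted complete-case analysis still carried about 0.10 of the 0.20 SD bias. Imputation from arm, baseline and age would do roughly the same, because there is only one follow-up measurement of the primary outcomes.

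**The case against.** A reader might infer that the bias probably favours the supplement, or that the 12% to 19% rejection rates are what to expect. The protocol supports neither.

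- **Direction.** The second cancellation criterion speaks of a woman being affected without saying whether for better or worse. Women in either arm may withdraw, and in an open trial those given nothing may leave too. Supplement-only exit is a feature of the cancellation criteria, not of drop-out in general.
- **Strength of the link.** The primary outcomes are lipids, uric acid, HbA1c, baPWV and visceral fat area, with no measurement between weeks 0 and 12, so nobody can leave in response to an interim value. Section 8 expects only rare allergic symptoms, and stopping for symptoms may have little to do with week-12 LDL cholesterol or fat area. Nothing in the protocol supports a correlation of 1.0, or indeed 0.5.
- **Wording.** The cancellation criteria open by saying that the research is discontinued, which could mean the whole study. Their place among the criteria for individual subjects, and their references to the subject, favour the per-woman reading without settling it. Drop-out is also undefined, so it is not certain that a woman who stops tablets but attends week 12 would be deleted.
- **Baseline objective.** Losing a few of 60 women from a correlation analysis costs little precision.

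These points stand and limit what can be said about direction and size. They do not rescue the sentence in section 7: even with voluntary withdrawal alone, deleting non-completers means the groups compared are not the groups randomised.

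**Conclusion.** The concern holds as a defect of structure. A fixed completers-only rule in an open randomised trial replaces the randomised comparison with one between women who stayed. The direction of any bias is unknown. Its size runs from zero, through about 0.10 to 0.14 SD, to a limit of about 0.19 to 0.27 SD. That range assumes 10% to 15% loss confined to the supplement arm, with a correlation between loss and outcome of 0, 0.5 and 1.0 in turn; the last is an extreme and not a forecast. Comparable, outcome-related loss in the no-supplement arm would offset some of it. The effect on the week-0 equol analysis is small and avoidable. For safety, the literal rule leaves out the women whose experience matters most.

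**What to change.** Replace the sentence in section 7 with text to this effect:

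1. All randomised women are analysed in the arm to which they were assigned.
2. Women who stop the supplement are still invited to the week-12 measurements, and those values are used. This is the main remedy, because it is the only step that removes bias from outcome-related stopping.
3. Values still missing are handled by a baseline-adjusted likelihood model or multiple imputation, stated to assume missing at random, with a sensitivity analysis for departures from that assumption. The completers-only result is a further sensitivity analysis.
4. Analyses that need only week-0 data use every woman who has them.
5. Safety includes every woman who took the supplement.

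The protocol should also define drop-out and make clear whether the cancellation criteria apply to the individual woman or to the whole study. The criteria themselves need not change for this purpose.

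The cost is protocol wording, a little more analysis work, and inviting women who stop to a visit already in the schedule. The estimate may be slightly diluted by non-adherence.
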